### Study Conduct

Eligible patients will be approached by research staff at the time of routine clinical visits or via telephone and provide informed consent. All of the participants’ concomitant medications will be continued during the study. Corticosteroids will be tapered at the discretion of the investigator. Addition of new IBD medications will be allowed during the study. If the new medication is an eligible oral or subcutaneous addition to existing therapy, this will be tracked using the approach that was used to track the original medication during the initial treatment. If the new medication replaces the initial therapy, the replacement medication will be similarly tracked.

Participants will be randomized 2:1 to receive either remote monitoring or standard of care using a random permuted block design with randomly varied block sizes. Participants will be stratified based on study site and disease subtype (CD vs UC or indeterminate colitis). We chose to stratify on these variables because they could affect the response to the intervention; stratification will ensure balance of these covariates among the study groups. The randomization order will be computer generated, and group assignment will be made when a new participant is enrolled into the study by the clinical site. The site investigators and research staff will remain blinded to the randomization order. The participants and physicians will not be blinded to the group assignment; however, we will attempt to minimize measurement bias by collecting outcome data through electronic data capture directly from participants.

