## Introduction

### Background

Inflammatory bowel diseases (IBDs), comprising Crohn disease (CD) and ulcerative colitis (UC), are chronic, progressive, inflammatory conditions of the gastrointestinal tract that affect up to 3 million Americans [1]. IBD is thought to be driven by inappropriate immune responses to an altered gut microbiome, with a disease course characterized by remitting and relapsing episodes of inflammation, or flares.

Most patients with a chronic condition require long-term therapy. Evidence has demonstrated that suboptimal adherence is associated with poor clinical outcomes, including increased IBD activity and associated complications, worsened quality of life (QoL) [2], and higher health care use and costs [3]. In addition, nonadherence to biologic therapies may increase the risk for developing antidrug antibodies, leading to loss of response to therapy. Despite this, adherence to IBD therapies remains suboptimal. A recent survey administered to 322 patients with IBD found that 55% reported nonadherence, including forgetting or skipping medication owing to not feeling well [4]. Overall adherence to IBD medications ranges from 40% to 80%, depending on the patient population, medication class, data sources, and adherence quantification measures [5].

Adherence to oral IBD medications such as aminosalicylates and thiopurines ranges from 50% to 93% [6]. Studies evaluating adherence to biologic therapies are conflicting. Using a medication possession ratio (MPR)—calculated as the number of days of supply of medication obtained during the observation period out of the total number days in the observation period—of <100% as a definition of nonadherence in 365 patients with IBD treated with biologic therapies, adherence was highest for intravenous formulations (70%-83%) compared with subcutaneous biologics (47%-50%) [7]. Conversely, in a large multicenter prospective cohort study where adherence was defined as ≥80% using a visual analog scale, the majority of patients with CD and UC were considered adherent (88% and 86%, respectively) [8]. However, when comparing across medication classes, adherence was lowest for patients on rectal (68%) and oral (83%) therapies and highest for intramuscular (88%) and parenteral (87%) therapies [8]. Similar results were found in a recent study of 112 patients with IBD in the Manitoba cohort: 81% of the patients were considered adherent to their therapy using an MPR cutoff value of ≥90% [9].

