We then pursued a 12-month randomized clinical trial to assess the effectiveness of the UC HAT system compared with best available care (BAC). We modified the symptom diary and alert criteria to make them specific to UC and added action plans and electronic messaging for participants to communicate with the research team. Adults with UC from the University of Maryland and Veterans Affairs Hospital in Baltimore were randomized to self-testing with the UC HAT system weekly or BAC. All participants underwent visits at baseline and every 4 months. Disease activity was measured using the Seo index [18,19], disease-specific QoL was measured using the Inflammatory Bowel Disease Questionnaire [20], and medication adherence was measured using a medication adherence scale [21]. We randomized 47 patients, and 29 (62%) completed the study. After adjustment for baseline QoL scores, participants in the UC HAT arm had a strong trend toward decreased Seo index scores from baseline (mean –11.9, SD 6.6; *P*=.08). Furthermore, after adjustment for baseline disease knowledge, participants in the UC HAT arm had a significant increase in QoL scores from baseline (mean 12.5, SD 5.9; *P*=.04), whereas participants in the BAC arm had nonsignificant decreases in QoL scores from baseline (mean –3.8, SD 5.3; *P*=.47). The difference in change in QoL scores from baseline between the UC HAT and BAC arms at 12 months was significant. Self-reported adherence to medical therapy was low in both groups at baseline (BAC: 45% and UC HAT: 40%). Adherence rates increased in both groups but were not significantly different at any time point after baseline. Both arms had poor IBD knowledge at baseline, with improvement at the 12-month follow-up; however, there was not a significant difference between the UC HAT and BAC arms at the 12-month follow-up [22]. Our results suggested that the randomization process was inadequate because participants in the UC HAT arm had higher rates of immune suppression use and greater impairments in QoL than participants in the BAC arm. We suspect that the baseline differences in favor of the BAC arm impaired our ability to demonstrate a treatment effect of the UC HAT system. This hypothesis is supported by the findings of clinically important improvements in disease activity and QoL from the baseline to the 12-month visit in the UC HAT arm. Furthermore, after adjustment for baseline disease knowledge, a significant improvement in QoL was noted in the UC HAT participants.

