### Study Population

Patients will be recruited for this study from 5 clinical centers at the University of Maryland School of Medicine, University of Cincinnati School of Medicine, NYU Grossman School of Medicine, University of North Carolina School of Medicine, and Vanderbilt University School of Medicine.

Inclusion criteria will include (1) aged ≥18 years; (2) documented IBD based on usual diagnostic criteria, including clinical symptoms and findings from endoscopy, radiology studies, and histology [30]; (3) initiation of treatment with a new oral or subcutaneous treatment for IBD; (4) access to a smartphone with a reliable data plan or Wi-Fi access; and (5) ability to understand the protocol and provide informed consent in English. Exclusion criteria will include (1) inability to speak and read English or comply with the study protocol; (2) the presence of an ileostomy, colostomy, ileoanal pouch anastomosis, or ileorectal anastomosis; (3) initiation of oral corticosteroids only without concurrent use of an oral or subcutaneous maintenance therapy; (4) imminent surgery within the next 60 days; (5) history of short bowel syndrome; or (6) uncontrolled medical or psychiatric disease.

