For oral medications, mean adherence <80% in a 2-week period will trigger an alert. For subcutaneous medications, 2 missed doses of adalimumab and 1 missed dose of other biologics will trigger an alert. If alerts are triggered for nonadherence, a clinical nurse, pharmacist, or social worker will contact the participant to identify barriers to adherence; remediation will be initiated, if possible. For participants with CD, a PRO-2 abdominal pain score of 2 (moderate) or higher or a liquid stool frequency score of >4 will trigger an alert. For participants with UC or IBD type undetermined, a rectal bleeding score of 2 or a stool frequency score of 2 will trigger an alert (obvious blood most of the time or blood alone passes and stool frequency >2 stools more than normal, respectively). A clinical nurse will contact the participant if a symptom-based alert is triggered.

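### The primary MPR comparison is an unadjusted t test; index-drug route (oral or subcutaneous) should be a prespecified covariate, not left to a baseline-difference check

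*Protocol article*

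**What the plan says.** The Study Population section admits patients on "initiation of treatment with a new oral or subcutaneous treatment for IBD". Under Study Conduct, "Participants will be stratified based on study site and disease subtype (CD vs UC or indeterminate colitis"). The reason given there, with its last words cut, is this: "We chose to stratify on these variables because they could affect the response to the intervention; stratification will ensure balance of these covariates among the".

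The Intervention Group section makes the intervention depend on the drug. Reminders and scans fall on the days when a dose is due. The nonadherence alert also differs by route: "For oral medications, mean adherence <80% in a 2-week period will trigger an alert", while for subcutaneous drugs the trigger is two missed doses of adalimumab or one of any other biologic.

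The Statistical Analyses section compares mean MPR between arms with t tests. Separately, baseline variables are compared between groups, and those found to differ are to be evaluated as potential confounders in regression models. No covariate is named, and the rule is not tied to the primary test.

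The Background section gives adherence by drug type. In one cohort, 83% of patients on oral therapy and 87% on parenteral therapy were adherent; in the same cohort the figures were 88% for Crohn disease and 86% for ulcerative colitis. Other figures there come from different studies with different definitions, and the section calls the evidence on biologics conflicting.

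**The concern.** The protocol's own reason for choosing strata applies to route. A participant on daily tablets is reminded and scans every day, and is flagged on a two-week average. A participant on an eight-week injection is prompted rarely and flagged after one missed dose. The number of contacts and the speed of detection therefore differ by route.

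Two things are at stake. First, whatever spread in MPR exists between routes stays in the residual variance of an unadjusted t test, so the confidence interval is wider than it need be even when the arms are balanced. Second, with only 41 controls the arms can differ by chance in their route mix, and part of the realised MPR difference would then reflect that mix.

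The baseline-difference rule is a weak safeguard. In a randomised trial the case for adjusting for a variable rests on how strongly it predicts the outcome, not on whether a baseline test happens to be significant. Choosing covariates that way also leaves the analysis model dependent on the data.

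**Working it through.** **The plan's own sample size.** Inputs (Statistical Analyses): rates 0.65 and 0.90, 2:1 allocation, type I error 0.05, power 0.90. I take the test as two-sided, with pooled variance and no continuity correction.
- Pooled rate = (2 × 0.90 + 0.65)/3 = 0.8167.
- Controls = [1.960 × √(1.5 × 0.8167 × 0.1833) + 1.2816 × √(0.65 × 0.35 + 0.90 × 0.10/2)]² / 0.25² = (0.929 + 0.669)² / 0.0625 = 40.8, rounded up to 41.
- Total = 41 + 82 = 123, as stated. Nothing below changes this number.

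**Assumptions.** The article gives no route mix, no MPR by route and no SD of MPR. I assume half the participants on injections (30% as a variant), a within-route SD of 0.25 to 0.30, and a route gap in mean MPR of 0.04 to 0.20. The lower gap borrows the 83% vs 87% comparison, which is a difference in the share of adherent patients and not in mean MPR. The upper gap is a deliberately large value that no study in the article establishes.

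**Chance imbalance in route.** SD of the difference in share = √[q(1 − q)(1/41 + 1/82)].
- q = 0.5: √(0.25 × 0.03659) = 0.0956, or 9.6 points.
- q = 0.3: √(0.21 × 0.03659) = 0.0877, or 8.8 points.

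Exact probabilities from two independent binomials (82 and 41):

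| Share on injections | At least 10 points | At least 15 points | At least 20 points |
|---|---|---|---|
| 50% | 0.28 | 0.11 | 0.035 |
| 30% | 0.24 | 0.08 | 0.021 |

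These treat route as unrelated to site and subtype. If route goes with disease subtype, the existing strata already balance part of it and the probabilities are lower.

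**Shift in the realised MPR difference** = imbalance × route gap. At 15 points:
- gap 0.04: 0.15 × 0.04 = 0.006
- gap 0.20: 0.15 × 0.20 = 0.03

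The planned difference is 0.25, so these are 2% and 12% of it. That 0.25 is itself a difference in adherence rates, used here as the only yardstick the article offers.

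**Would the baseline rule catch it?** If a difference counts as detected at p < 0.05 (assumed), the threshold at q = 0.5 is about 1.96 × 9.56 = 18.7 points. A 15-point imbalance would not trigger adjustment.

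**Variance left in the error term.** At a 50:50 mix, between-route variance relative to within-route variance = 0.25 × gap² / SD².
- gap 0.20: 0.01/0.0625 = 16% (SD 0.25); 0.01/0.09 = 11% (SD 0.30)
- gap 0.04: 0.0004/0.0625 = 0.6%; 0.0004/0.09 = 0.4%

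Standard error of the MPR difference at within-route SD 0.25, where √(1/41 + 1/82) = 0.1913:
- route in the model: 0.25 × 0.1913 = 0.048
- route ignored, gap 0.20: √(0.0625 + 0.01) × 0.1913 = 0.052
- route ignored, gap 0.04: √(0.0625 + 0.0004) × 0.1913 = 0.048

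**Type I error of the unadjusted t test.** In 40,000 simulated trials with no effect (gap 0.20, within-route SD 0.20, half on injections), it was 0.050 overall, 0.051 among trials with an imbalance of 8 to 12 points, and 0.12 among those with 18 to 22 points.

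**The case against.** The case on the other side is substantial.

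- **No bias on average.** A reader might infer that leaving route unstratified biases the comparison. It does not: the simulated type I error is 0.050, and the t test's standard error already allows for chance imbalance. An imbalance near 10 points is close to harmless. This stands; the argument concerns precision and the single realised trial.
- **No large route gap is documented.** A reader might take a gap of 0.2 or more from the Background section. The one comparison within a single study that bears on this is 83% vs 87%. The low subcutaneous figures are set against intravenous drugs, which are not eligible index drugs, and count any MPR below 100% as nonadherence. All these figures are shares of adherent patients, not mean MPRs. This stands, and is why the range starts at 0.04.
- **The earlier trial is not a precedent for route.** The article says of it: "Our results suggested that the randomization process was inadequate because participants in the UC HAT arm had higher rates of immune suppression use", and adds worse quality of life. Immune suppression is not route, since thiopurines are listed among the oral drugs, and the authors only suspect an effect. The earlier trial supports taking baseline treatment seriously, no more.
- **The chosen strata are defensible.** Disease subtype also changes the intervention, through the PRO-2 items and symptom alerts, and the article does not claim that its strata are exhaustive. This stands. Adding route would make 20 cells of about 6 participants (123/20), against 10 of about 12 now.
- **Covariates may sit in an analysis plan not shown.** This is fair for omitted detail. But the article does fix an unadjusted t test and a data-driven confounder rule, and those stated choices can be criticised as they are.
- **Binary route is coarse.** Alert rules differ within subcutaneous drugs, and drugs may be replaced during the year. This limits the gain but is no reason to ignore a variable known at enrolment.

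**Conclusion.** The concern holds as a weakness of the primary analysis, of minor to moderate weight. The plan pairs an unadjusted t test with covariate selection by baseline comparison, while a variable that alters how the intervention works, and may affect adherence, is neither a stratum nor prespecified.

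The trial is not biased on average, and the likely distortion is small against 0.25. It would matter more if the true MPR effect were smaller than planned. The precision gain runs from negligible at a gap of 0.04 to a standard error about 7% lower at a gap of 0.20 (0.048 vs 0.052, from unrounded 0.0478 and 0.0515). All sizes rest on the assumed route mix, gap and SD. The documents do not support reading this as a flaw in the randomisation.

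**What to change.** Keep the current randomisation strata. Replace the primary t test with a linear model for MPR that includes arm, the two stratification factors (site and disease subtype) and index-drug route as recorded at randomisation. Fix these terms in advance, whatever the baseline comparison shows, and drop the rule of choosing confounders from detected differences for the primary analysis. Route must be the value at randomisation, because drugs can be added or replaced later. Report the MPR difference within each route descriptively.

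The cost is one degree of freedom for route and five for the strata (four for site, one for subtype), out of 123 participants. Route is known at enrolment, so no new data are needed, and the sample size is unchanged. If the route gap is small, the gain in precision will be small too.

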### Intervention Group

Eligible patients will complete a baseline survey gathering demographic and clinical information. Upon enrollment, the intervention participants will activate their account to access the patient-facing Tappt web application, which includes the individual participants’ medication regimen information, upcoming doses, and adherence data. The web application also includes a curated resource library with links to educational material on the Crohn’s and Colitis Foundation website, expert-led video modules on each IBD medication class, and training videos on how to use the system and seek support. The web application also allows patients to respond to surveys related to nonadherence or PROs. The system uses algorithms to send participants personalized alerts and reminders for medication doses or survey completion through SMS text messages.

After providing training to the intervention participants on how to use the Tappt system, the research team will input into the system the intervention participants’ deidentified information as well as the medication to be tracked, dose, and frequency of dosing. The research team will then assign smart labels to the participants’ medication regimen, which will be used by the participants to record their medication use. The research team will also walk each study participant through the Tappt system and explain how to label and scan medication and how to complete all required surveys. Along with the first medication, the corresponding smart labels to be affixed to the pill bottle, pen, or syringe container of the newly prescribed medication will be shipped to the participants. Participants will receive sufficient labels for dosing of 90 days of the medication to be tracked, plus an additional 2 to 6 labels to account for lost or damaged labels and dose escalation. Participants will receive enough labels until their next assessment (ie, a participant on mesalamine 2.4 g daily will receive 90 labels). Changes in dose of medications for the intervention participants will be monitored on a weekly basis by study coordinators. Any change in dosing will be updated on the Tappt clinician portal; labels will be reassigned to the new dosing frequency, and a new set of smart labels will be sent to the participants for the next 90-day dosing period.

At the time of taking a medication dose, participants will scan the label with their mobile phone to verify that they are taking the medication. Upon scanning, participants will immediately receive a notification on their device indicating that the label was successfully scanned and that their medication adherence was updated in their profile. Each day that a medication is due to be taken, participants will receive a reminder through SMS text message notifying them of their medication schedule for the day. If participants fail to scan the label at a given time (as determined by their specific medication regimen), they will receive an SMS text message at the end of the day with a link to respond to a survey that captures reasons for nonadherence.

Participants will also complete a PRO-2 assessment at baseline and then monthly for the entire 12 months of the study triggered by the Tappt system through an HTML link sent to patients by SMS text message [31,32]. For participants with CD, the PRO-2 assessment includes abdominal pain and liquid stool frequency. For participants with UC or indeterminate colitis, the PRO-2 assessment includes rectal bleeding and stool frequency. The research team will also be able to send the PRO-2 survey to patients at any given time, at their discretion, if patients are experiencing a flare or at the time of a change in medication dose. Items for the PRO-2 assessment vary based on disease type (refer to the Outcomes and Outcome Measures section).

Clinical teams can review their participants’ data in real time through the secure cloud-based provider-facing Tappt portal. To reduce monitoring burden among clinical teams, the system’s algorithms prompt automated email alerts to the clinical team when participants’ adherence or PROs fall below predetermined thresholds, when a participant’s regimen is approaching refill date, or when a participant reports an error on their profile. These alerts can support clinical teams in following up with patients in a timely manner to reduce risk for poor outcomes (Figure 1).

For oral medications, mean adherence <80% in a 2-week period will trigger an alert. For subcutaneous medications, 2 missed doses of adalimumab and 1 missed dose of other biologics will trigger an alert. If alerts are triggered for nonadherence, a clinical nurse, pharmacist, or social worker will contact the participant to identify barriers to adherence; remediation will be initiated, if possible. For participants with CD, a PRO-2 abdominal pain score of 2 (moderate) or higher or a liquid stool frequency score of >4 will trigger an alert. For participants with UC or IBD type undetermined, a rectal bleeding score of 2 or a stool frequency score of 2 will trigger an alert (obvious blood most of the time or blood alone passes and stool frequency >2 stools more than normal, respectively). A clinical nurse will contact the participant if a symptom-based alert is triggered.

**Figure 1 figure1:**
[figure not shown]
Study intervention: the Tappt remote therapy monitoring digital health system.

### Control Group

The standard of care for participants in this study is modeled after the standard of care at all study sites. Standard of care is based on current evidence-based guidelines, including a comprehensive assessment, a guideline-concordant therapy plan, scheduled and as-needed clinic visits, scheduled and as-needed telephone calls, and administration of educational fact sheets about disease-specific topics when appropriate. Personnel used to provide standard of care at each site will vary and may include nurse coordinators, advanced practice providers, social workers, psychologists, dietitians, pharmacists, and other ancillary staff.

